### Policy tracer studies

Policy tracer studies will be conducted post intervention to examine policy change and track the influence of research retrospectively. These studies will also examine the feasibility and utility of using such methods to provide outcome data, and if successful to investigate the influence of research on policy [26]. The tracer studies will examine policy change and track the influence of research retrospectively. They will be conducted in 4 purposively selected intervention councils at the conclusion of the intervention. The sampling frame will consider council size and structure and engagement with KT4LG as monitored by the study team. Councils who agree to participate will select a policy change and in-depth interviews with key actors across council will be conducted by the KB. The focus of the interview will be to explore the lead-up to the decision, why the decision was made, who was involved, and what evidence was useful and influential. This will be combined with document analysis of meeting minutes, policy drafts and project plans where available.

### Impact evaluation

Regular monthly meetings and training sessions with intervention councils will be used as opportunities to explore the impact of the value of the intervention. Intermediary outcomes of interest include skills in using research evidence and combining with other sources of evidence, access to research evidence, and confidence in using research evidence. Site visits will be conducted at the one-year point of the intervention with participating councils (November 2010) and repeated again at the conclusion of the intervention (November 2011). During these visits, tools that focus on exploring stages and levels of evidence utilisation at both individual and organisational levels will be used to assess research use [27,28]. Data will be collected by the KB during these face to face meetings and analysed by RA under the guidance of the research team. Evaluation of training sessions will also be conducted and will contribute to the impact evaluation.

### Process evaluation/measures

The process evaluation will seek to capture information related to the intensity (dose), fidelity and reach of the intervention. Measures of context, staff turnover, barriers, facilitators, quality of engagement, which are likely to be useful in assessing acceptability and helping to modify the logic model and intervention content/delivery will be captured. An Access database has been developed to collect this data.

Measures of adoption will include:

▪ Number of councils involved - intervention and control

▪ Number of councils attending each training session

▪ Number of councils adopting our materials, frameworks (including EIDM and also determinants approach to obesity prevention)

▪ Other organizations adopting intervention materials

▪ Departments across council adopting our materials, frameworks

▪ Number of councils participating in monthly contact

▪ Number of councils that don't participate and why

▪ Demographics of participating councils

▪ Cost of the intervention to councils

Measures of reach will include:

▪ Number of participants from each council attending training sessions

▪ Number of people participating in monthly contact (which department)

▪ Number of people attending research symposium

▪ Number of additional stakeholders involved

▪ Resources distributed

▪ Characteristics of participants (job description, position title)

▪ What helped and hindered participation by individuals

▪ Characteristics of non-participants

Measures of implementation will include:

▪ Number of monthly contacts

▪ Number of training sessions

▪ Number of forums

▪ Requests for attendance at meetings

▪ Participant satisfaction (evaluation of training sessions and research symposium)

▪ Delivery of training sessions compared to expected delivery

▪ Delivery of monthly contact compared to expected delivery

▪ Why/why not are resources used by participants

▪ Cost of implementation (to researchers)

▪ Timeliness of intervention delivery (do we stick to our timeline)

▪ Quality of delivery

▪ Any issues raised during implementation - and how were these addressed

▪ Delivery of intervention components as planned

### Economic evaluation

In addition, an economic evaluation will help to answer the key questions of whether the intervention is affordable (i.e. gross/net cost) and whether it offers value-for money. Pathway analysis will be used to identify the resources associated with each arm. These resources will be valued using the most up-to-date sources for the 2010 reference year. The incremental or net intervention cost will equal the difference in costs between the two intervention arms. The consequences of the intervention will be measured in terms of willingness-to-pay (WTP) in a cost-benefit analysis (CBA). A CBA compares the net costs of the intervention to the dollar value of the identified outcomes.

### Data management and analysis

Quantitative data will be collected using the EIDM survey. Participant responses will be collected using Survey Monkey [29] and then transferred to Stata for analysis [30].Baseline characteristics of intervention and comparison councils and staff will be compared. Summary statistics for each outcome, broken down by group, will be presented at follow-up, with 95% confidence intervals appropriately adjusted for clustering (Stata svy procedures).

The primary analysis for assessment of the effect of KT4LG on primary outcomes would be ascertained in a large scale trial using a council-level weighted regression model with the stratification variable (budget tertile) and baseline measures included as covariates, It is acknowledged that the sample size in this exploratory trial is small and therefore provide imprecise effect estimates (and 95% confidence intervals). More usefully, the data from this study will be analysed to provide estimates of the intracluster correlation for each outcome, which will be calculated using analysis of variance (Stata loneway), and of standard deviations and correlations of baseline and follow up measures (council and staff level).

Qualitative data will be collected in a variety of ways but will predominantly involve key informant interviews and process diaries maintained by the KB. Key informant interviews will be tape-recorded and transcribed verbatim. Given the lack of one theoretical approach to guide this work, a grounded theory approach will be used to inform qualitative data analysis [31-33]. The qualitative data will be coded and categorised using N-Vivo software [34] to identify emerging patterns and themes. While this study seeks to influence the use of research evidence it is acknowledged that other types of knowledge also inform decision-making. The process evaluation will collect this information and will also explore the influences on decision-makers [35].

Data collection for the economic evaluation will be closely integrated in the process evaluation, described earlier. A questionnaire will be administered to stakeholders from each of the participating councils (both intervention arms) at the conclusion of the intervention. It will ask a series of questions to ascertain the maximum amount which a council would be willing to pay (WTP) to have access to the KT4LG intervention. The questionnaire will be piloted in face-to-face format as part of the tracer study interviews. The usefulness of the WTP method in assessing value attached to the KT4LG intervention will be assessed both for specific examples (the tracer studies) and as a generic question. To avoid operator bias, the delivery of the intervention and the collection and analysis of data will be separated. Where data is collected, the KB will be responsible for data collection but will not be involved in data analysis. The project team will be supported by the scientific research team comprised of the chief and associate investigators who will advise on scientific and ethical issues. To monitor adverse effects of the intervention, we will be examining this issue with councils at mid point and completion of the study.

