**Figure 1 F1:**
[figure not shown]
**Proposed study timetable**.

3. What are estimates of intra-cluster correlation by council of outcomes and of the change in such outcomes that a larger trial would need to be powered to detect?

In order to answer these questions this research program has 2 key aims:

1. Undertake an exploratory cluster randomised controlled trial to identify acceptability of the multi-component knowledge translation and exchange model, identify potential modifications, estimate key parameters required for a full scale trial including recruitment procedures, recruitment and retention rates, variation in outcome measures, intra-cluster correlation coefficients, and estimate feasible effect sizes and intervention costs for a full scale trial.

2. Develop recommendations about KT models applicable to local government settings and specific recommendations for the value and design of a large scale trial.

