#### Comparison councils

The comparison councils will receive access to summaries of intervention research. These will be circulated by email to all participating councils.

This research program will incorporate two of the phases in the UK Medical Research Council's (MRC) framework for evaluating complex interventions: Phase I and Phase II [19]. The developmental research program involved development of the intervention's components, based on existing evidence, survey data and key informant interviews.

This paper reports on the design of the intervention trial, which is being conducted in 28 councils (14 randomised to participate in the intervention and 14 to act as comparison councils). This will inform the development of a case for a possible future Phase III trial [19].

Ethical approval for this project was granted by the University of Melbourne Human Ethics Committee [ref 0722362).

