### Recruitment and randomisation of local governments

#### Baseline survey

All 79 Victorian local governments were invited to participate in a state-wide baseline survey. Individuals that were employed by Victorian local governments and involved in public health were eligible for participation. Up to four people from each local government were invited to complete an online survey. The survey aimed to elicit how local governments currently make decisions, the contribution of research evidence to decision-making, the facilitators and barriers to EIDM to identify strategies already in place that support evidence-informed decision-making and to explore additional strategies that might support EIDM. One hundred and thirty six responses from 45 local governments were received. Reasons for non-participation included workload, staffing issues (e.g. positions currently vacant), and a recent bushfire disaster. Many of those unable to participate said that they supported the study and asked to be kept informed of the outcomes. Only those local governments who agreed to participate in the initial survey were invited to participate in the trial.

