#### Randomisation

Stratified block randomisation was used to randomly allocate participating councils to intervention or comparison group. Strata were defined by tertile of council's annual budget. Analysis of the baseline survey revealed a linear relationship between budget and population size which suggested that either could be selected as the stratification variables. Given the anticipated resource implications of practicing EIDM (e.g. staffing resources, access to internet and other resources), council budget was deemed to be most appropriate. Each intervention council then nominated a number of staff to participate in the intervention, ideally those who participate in public health planning. Once participation was agreed and a memorandum of understanding was signed, the programme coordinator emailed the trial manager with the name and annual budget of the council. The trial manager then emailed the trial statistician with the stratum (but not name) of the council. The statistician then allocated the council (blind to its identity) to intervention or comparison on the basis of a randomisation sequence of block size 4 generated and held by the trial statistician and concealed to all other parties. The trial manager logged the group allocation on the trial database and informed the program coordinator.

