### Sample size

Given that the outcome measures had not previously been employed precise sample size calculations, whilst broadly estimated a priori, were unable to be undertaken in the absence of estimates of standard deviation and intra-cluster correlation. However, this study will provide estimates of SD and ICC.

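### The one-way ANOVA ICC counts any budget-tertile difference, and any intervention effect if the arms are pooled, as between-council variance, so it does not match the adjusted model named for the large trial

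*Protocol article*

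**What the plan says.** The trial is exploratory, in "28 councils (14 randomised to participate in the intervention and 14 to act as comparison councils". One research question, under Aims and objectives, is "What are estimates of intra-cluster correlation by council of outcomes". The Sample size section explains that precise calculations "were unable to be undertaken in the absence of estimates of standard deviation and intra-cluster correlation" and says this study will supply those estimates.

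Under Data management and analysis, the article concedes that effect estimates will be imprecise. It presents as more useful the "estimates of the intracluster correlation for each outcome, which will be calculated using analysis of variance (Stata loneway". It also plans to report SDs, and how strongly the two survey waves correlate, for councils and for staff. The EIDM survey section links estimation of SD and ICC to the post-intervention survey. Neither section says whether the arms are pooled or analysed separately.

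The same analysis section says that a large trial would use a "council-level weighted regression model with the stratification variable (budget tertile) and baseline measures included as covariates". On allocation, the Randomisation section says "Strata were defined by tertile of council's annual budget".

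**The concern.** A one-way ANOVA by council has a single factor. Every systematic difference between councils goes into the between-council mean square, whatever its cause. After the intervention there are two identifiable causes besides ordinary clustering: the arm a council was in, and its budget tertile. The large trial's model would estimate the first and adjust for the second, so neither belongs in the ICC used to size it.

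At stake is a planning figure that the article itself ranks above the effect estimate. If it is too high, the next trial is made too large. No inference within this trial depends on it.

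**Working it through.** **Inputs from the protocol article.** 28 councils, 14 per arm; three budget strata; and "One hundred and thirty six responses from 45 local governments were received", which gives 136/45 = 3.02 respondents per council. I take m = 3. There is no stated ICC, SD, effect size or sample size to reproduce.

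**Assumptions.** Total variance within arm and stratum = 1; true ICC ρ = 0.05; arm effect d = 0.3 or 0.5 SD; adjacent-tertile step t = 0 or 0.3 SD; stratum split 8/12/8 unless stated.

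**Variance added between councils (arms pooled).**
- Arm: Va = (d²/4)(28/27). For d = 0.3, 0.0225 × 1.037 = 0.0233. For d = 0.5, 0.0625 × 1.037 = 0.0648.
- Tertile means −t, 0, +t: Vt = 16t²/27. For t = 0.3, 16 × 0.09/27 = 0.0533.

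**Expected one-way ICC** = (ρ + Va + Vt)/(1 + Va + Vt). **Design effect** = 1 + (m − 1) × ICC, compared with 1 + 2 × 0.05 = 1.10.

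| Case | Expected ICC | Design effect | Ratio to 1.10 |
|---|---|---|---|
| no arm or tertile effect | 0.050 | 1.100 | 1.00 |
| d = 0.3 | 0.0733/1.0233 = 0.072 | 1.143 | 1.04 |
| d = 0.5 | 0.1148/1.0648 = 0.108 | 1.216 | 1.11 |
| t = 0.3 only | 0.1033/1.0533 = 0.098 | 1.196 | 1.09 |
| d = 0.3, t = 0.3 | 0.1267/1.0767 = 0.118 | 1.235 | 1.12 |
| d = 0.5, t = 0.3 | 0.1681/1.1181 = 0.150 | 1.301 | 1.18 |

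The last row depends a little on the stratum split. With 10/9/9 councils, Vt = (19 − 1/28) × 0.09/27 = 0.0632, the ICC is 0.1780/1.1280 = 0.158, the design effect 1.316 and the ratio 1.20.

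**Simulation (28 councils, 3 respondents each, 6,000 replicates).** The mean one-way ICC was 0.070 for d = 0.3, 0.103 for d = 0.5, and 0.145 for d = 0.5 with t = 0.3. With only the arm removed and t = 0.3, it stayed at 0.095 to 0.098. With arm and tertile both removed, it was 0.045 to 0.049 in every case.

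**Sampling error.** SE = √[2(1 − ρ)²(1 + (m − 1)ρ)²/(m(m − 1)(k − 1))]. For ρ = 0.05 and m = 3 the numerator is 2 × 0.9025 × 1.21 = 2.184.
- k = 28: √(2.184/162) = 0.116. The simulated SD is about 0.12, with a 95% range of about −0.18 to 0.28.
- k = 14 (one arm alone): √(2.184/78) = 0.167.
- k = 45 (baseline survey): √(2.184/264) = 0.091.

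The arm-only bias at d = 0.5 (0.108 − 0.05 = 0.058) is about half the sampling SD. The largest bias considered (0.158 − 0.05 = 0.108) is still slightly below it.

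**Effect on a next trial (80% power, two-sided 5%, m = 3).** For a target of 0.3 SD, 175 people per arm are needed before clustering. Then 175 × 1.10/3 gives 65 councils per arm, against 67 at ICC 0.072 and 71 at 0.108.

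**The case against.** The strongest reply is that the text does not say the arms are pooled. Running the ANOVA within each arm would remove the arm component, and a condensed article may leave that detail to an analysis plan. This stands, so the arm part is conditional. The tertile part is not met by it, and by-arm use raises the SE from 0.116 to 0.167.

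The stated question asks for correlation by council, which an unadjusted ICC answers. The planned baseline and follow-up correlations at council and staff level also let a designer allow for baseline adjustment. Both points stand in part, but neither removes arm or tertile.

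Every effect size above is assumed. A step of 0.3 SD means 0.6 SD from the lowest to the highest tertile, for which the documents give no basis. Imprecision is shared by any estimator from these councils and is not a fault of the ANOVA.

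Stronger readings are tempting but not supported:
- *That the next trial would look infeasible because the state has only 79 councils.* At a target of 0.3 SD the unbiased ICC already calls for 2 × 65 = 130. At 0.5 SD (63 people per arm before clustering) the totals are 48 unbiased, 52 with arm bias and 56 with arm and tertile bias, all below 79. The conclusion could turn only in a narrow band between these targets.
- *That the inflation is larger.* Four staff per council, the most invited to the baseline survey, gives larger ratios (1.323/1.15 = 1.15 for d = 0.5), but the observed average was about 3.
- *That the Sample size section is wrong because the baseline survey could supply SD and ICC.* That section explains why calculation beforehand was not possible with measures not previously used, and the measures were developed from that survey. Its estimates would be a useful addition, not the correction of a false statement.
- *That the ICC is the trial's main deliverable.* It is one of several parameters, beside acceptability, recruitment, retention, effect sizes and costs.

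**Conclusion.** The point holds in limited form. The article fixes a one-factor estimator and links it to post-intervention data. That estimator takes in any tertile difference, and any intervention effect if the arms are pooled, so it does not give the residual ICC for the adjusted model described beside it. Under the assumed values a true ICC of 0.05 would be estimated at about 0.07 to 0.16 on average, and the design effect at about 3 respondents per council would be 4% to 20% too high. With no arm or tertile effect the bias is nil. It is conservative and smaller than the sampling error. That size does not excuse a systematic error that can be avoided from the same data. Severity is moderate, not must-fix.

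**What to change.** State that the ICC and SD for each outcome will be estimated from a two-level mixed model (or an ANOVA) that includes arm and budget tertile, both with and without the baseline measure, and reported with 95% confidence intervals.

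Also report the ICC and SD from the 45-council baseline survey. It carries no intervention effect and has more clusters. Budget tertile should be included there too, because a one-way estimate from that survey would still absorb it. Note beside it that intervention staff were nominated after allocation, so follow-up respondents may differ from those surveyed at baseline.

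The cost is a few lines of analysis and wording, and three between-council degrees of freedom (27 falls to 24: one for arm, two for tertile). No new data are needed.

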**Methods/Design:**

This paper describes the methods for KT4LG, a cluster randomised controlled trial which is exploratory in nature, given the limited evidence base and methodological advances. KT4LG aims to examine a program of KT strategies to increase the use of research evidence in informing public health decisions in local governments. KT4LG will also assess the feasibility and acceptability of the intervention. The intervention program comprises a facilitated program of evidence awareness, access to tailored research evidence, critical appraisal skills development, networking and evidence summaries and will be compared to provision of evidence summaries alone in the control program. 28 local governments were randomised to intervention or control, using computer generated numbers, stratified by budget tertile (high, medium or low). Questionnaires will be used to measure impact, costs, and outcomes, and key informant interviews will be used to examine processes, feasibility, and experiences. Policy tracer studies will be included to examine impact of intervention on policies within relevant government policy documents.

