## Methods/Design

### Study design

The study design is a cluster randomised controlled trial where local governments (councils) are randomised to intervention or control.

The intervention consists of two core components: 1. improved access to research evidence via provision of summaries of intervention research on topics of relevance in childhood obesity prevention for local government; and 2. building capacity of local governments to use research evidence to inform public health decision-making by providing facilitated support. Control (comparison) councils will receive component 1 and intervention councils will receive both components. The duration of the intervention will be two years. Figure 1 outlines the proposed study timetable.

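### As worded, the cost-benefit analysis sets willingness to pay for the two-component intervention against a net cost that covers essentially the facilitated support alone

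*Protocol article*

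**What the plan says.** The Study design section defines what is being evaluated: "The intervention consists of two core components: 1. improved access to research evidence via provision of summaries of intervention research", followed by facilitated capacity building as the second component. It then fixes the contrast: "Control (comparison) councils will receive component 1 and intervention councils will receive both components". The abstract agrees, listing summaries within the intervention program: "networking and evidence summaries and will be compared to provision of evidence summaries alone in the control program". On delivery of the summaries, the Comparison councils section says: "These will be circulated by email to all participating councils".

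The Economic evaluation section gives the cost side: "The incremental or net intervention cost will equal the difference in costs between the two intervention arms". It says the consequences will be expressed as WTP, and it states the comparison rule: "A CBA compares the net costs of the intervention to the dollar value of the identified outcomes".

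The Data management and analysis section gives the purpose of the WTP questionnaire, which goes to stakeholders in both arms at the end of the intervention: "to ascertain the maximum amount which a council would be willing to pay (WTP) to have access to the KT4LG intervention". The article does not restrict this to the increment over summaries, does not subtract the value of the summaries, and does not say how the two arms' answers will be combined.

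**The concern.** A cost-benefit analysis is interpretable only if the benefit and the cost refer to the same change. The cost here is incremental: the summaries go to both arms, so their cost drops out of the difference. The benefit, on the article's own definition of the intervention, is the value of the whole package. Credit would then be taken for the summaries without charging for them.

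The trial's contrast is facilitation plus summaries against summaries alone. Whether the program offers value for money is one of the two questions set for the economic evaluation, and the study's aims include advising on the value and design of a large-scale trial. A benefit figure that includes the summaries does not answer the question the randomisation poses, and any error from this source favours facilitation.

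There is also a difficulty with the respondents. Intervention councils have experienced both components. Comparison councils already hold the summaries and have not experienced facilitated support. The same question may therefore be answered about different things in the two arms.

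**Working it through.** The document states no cost, WTP or net-benefit figure, so there is nothing to reproduce. The check is algebraic, followed by an illustration on assumed units.

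**Notation**
- C1, C2: cost of the summaries and of the facilitated support.
- W12: maximum WTP for both components together.
- W1: maximum WTP for the summaries alone.

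**Step 1: cost side.** The intervention arm costs C1 + C2 and the comparison arm costs C1. Net cost = (C1 + C2) − C1 = C2. This assumes that circulating the summaries costs the same per council in each arm, which fits their common email delivery.

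**Step 2: benefit side.** Under the Study design definition, WTP for access to the intervention is W12.

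**Step 3: net benefit under three rules**
- As worded: W12 − C2.
- Consistent incremental: (W12 − W1) − C2.
- Consistent gross: W12 − (C1 + C2).

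The as-worded result exceeds the incremental one by W1 and the gross one by C1. A maximum WTP and a cost are both at least zero, so on this reading the error cannot go against the intervention. Because the increment is defined as W12 − W1, no assumption that the two values add is needed.

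**Step 4: illustration, assumed units only.** Take W12 = 100 and C2 = 80. As worded, net benefit is 100 − 80 = 20 and the benefit-cost ratio is 100/80 = 1.25.

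| W1 | Incremental net benefit, 100 − W1 − 80 | Ratio, (100 − W1)/80 |
|---|---|---|
| 0 | 20 | 1.25 |
| 10 | 10 | 1.125 |
| 20 | 0 | 1.00 |
| 30 | −10 | 0.875 |
| 50 | −30 | 0.625 |

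| C1 | Gross net benefit, 100 − 80 − C1 | Ratio, 100/(80 + C1) |
|---|---|---|
| 0 | 20 | 1.25 |
| 10 | 10 | 1.11 |
| 20 | 0 | 1.00 |
| 50 | −30 | 0.77 |

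With these units the sign turns negative only when W1 (or C1) exceeds 20.

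**Step 5: mixed answers.** Suppose the 14 intervention councils state W12, the 14 comparison councils state only W12 − W1, and all 28 answers are averaged. The mean is W12 − W1/2, so the excess over the incremental value is W1/2: 5, 10, 15 and 25 for W1 of 10, 20, 30 and 50. The overstatement halves, but the average then describes neither the package nor the increment.

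**The case against.** The strongest reply is that the article does not show the WTP items. It gives their purpose and says there will be several questions; these may already separate the summaries from the support. An article may properly leave questionnaire wording to the full protocol. Usage of the trial name also varies: in Data management and analysis, the regression is described as assessing the effect of KT4LG, which can only be the between-arm effect. On that usage the WTP object could be the increment, matching the net cost. Comparison councils, who already receive the summaries, might naturally answer that way. Costs are to be identified for each arm and gross cost is mentioned under affordability, so a gross comparison could be made. Finally, the trial is exploratory, and the questionnaire is to be piloted and the usefulness of the WTP method assessed.

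Much of this stands. A reader might infer that the analysis will overstate value for money, or will show facilitation to be worthwhile when it is not. The document does not support that: the question wording is unknown, the sign change above comes from chosen units, and at lower values of W1 the sign does not change.

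What remains is a mismatch between things the article does state. Its only explicit definition of the intervention includes the summaries, and its comparison rule specifies net rather than gross cost. If the trial name carries two meanings, the WTP object is ambiguous and still needs fixing. The pilot may not reveal this, because it is placed in the tracer-study interviews, which are confined to four intervention councils; no comparison council is included.

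**Conclusion.** The point holds in conditional form. Taken as written, the stated WTP object and the stated cost rule rest on different bases. If respondents value both components, net benefit is too high by W1 against a consistent incremental analysis, or by C1 against a consistent gross one. If comparison councils value only what they lack, a pooled WTP mixes two objects. If every respondent is in fact asked about the increment alone, there is no error.

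The size cannot be determined from the document, and the illustrative figures show only the mechanism. It would go too far to conclude that value for money is overstated as a fact, or that the economic conclusion would reverse. Nor is asking both users and non-users a fault in itself; the problem is leaving open what each is valuing. For a secondary economic analysis in an exploratory trial this is worth correcting, and it does not touch the main effect or intracluster correlation estimates.

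**What to change.** Put benefit and cost on one basis and say so in the plan, in one of two ways.

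1. **Incremental (matches the trial's contrast).** Define the WTP object as facilitated support over and above the summaries that all councils receive. Alternatively, elicit WTP for the summaries alone and for both components, and use the difference. Set this against the between-arm net cost.
2. **Gross.** Keep WTP for the whole package and compare it with the gross cost of both components. This needs the cost of the summaries but no subtraction of WTP, provided that all respondents are clearly asked about the whole package.

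Under either option, give comparison councils a short description of the facilitated support before they answer, report WTP by arm, and state how the two arms' answers enter the analysis. Including a comparison council in the pilot would test whether the question is understood there.

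The cost is rewording or adding one or two items in a questionnaire planned for the end of the intervention. The downside is a slightly more complex question.
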